## Abstract

**Introduction:**

Patients with concurrent obesity, type 2 diabetes, and depression experience high disease severity and prevalence. This triad of conditions compromises quality of life and treatment adherence, further exacerbating disease progression. Therapeutic strategies for such patients must address both glycemic control and psychological well-being. Liraglutide, a glucagon-like peptide-1 receptor agonist (GLP-1RA), offers benefits beyond glucose-lowering and weight reduction, with emerging evidence suggesting it may also alleviate depressive symptoms. Therefore, liraglutide represents a promising intervention for managing depression in patients with obesity and diabetes.

**Objectives:**

This study aims to assess the therapeutic efficacy of liraglutide in overweight or obese patients with type 2 diabetes and comorbid depression, with a specific focus on its antidepressant effects.

**Methods:**

This is a randomized, double-blind, placebo-controlled pilot trial. Sixty eligible participants will be randomly assigned (1:1) to receive either liraglutide (initiated at 0.6 mg/day, titrated weekly to a maximum of 1.8 mg/day) or a matched placebo, as an adjunct to standard care for 12 weeks. The primary endpoints include blood glucose levels, glycated hemoglobin, body mass index, Hamilton Depression Rating Scale score, and metrics derived from resting-state functional magnetic resonance imaging (resting-state fMRI). Secondary endpoints will assess changes in inflammatory biomarkers (tumor necrosis factor-α, interleukin-6), oxidative stress indicators (superoxide dismutase, malondialdehyde), homeostasis model assessment of insulin resistance, insulin sensitivity index, and homeostasis model assessment of β-cell function.

**Conclusions:**

This trial will provide preliminary data on the effects of liraglutide on depressive symptoms in overweight/obese patients with type 2 diabetes. The findings are expected to provide a basis and reference for subsequent large-scale clinical research.

## Introduction

### Background and rationale {6a}

Metabolic disorders, particularly obesity and diabetes, have become increasingly prevalent; recent epidemiological studies indicate that the global population affected by obesity has exceeded 2 billion (1), while the prevalence of diabetes is also on the rise (2).Today, type 2 diabetes(T2DM) and obesity are widely recognized as “co-occurring diseases” resulting from the interplay of genetic and environmental factors. Furthermore, overweight and obesity play a critical role in the development and progression of T2DM (3, 4). Notably, both obesity and T2DM are not only significant risk factors for disability and mortality, but also have a profound impact on emotional well-being (5).Research shows that metabolic diseases and mental disorders (especially depression) have a bidirectional relationship (6, 7).The risk of depression in patients with T2DM is 2–3 times higher than that in the general population, and the risk of developing T2DM in patients with depression is also significantly increased (8). A survey study found that the rate of depressive symptoms in patients with T2DM was as high as 68.2% (9), and an overweight/obese status may further increase the risk of emotional disorders in this group (10). Obesity and type 2 diabetes are considered physiological and psychosomatic diseases closely related to psychological factors (11).

Since metabolic diseases, such as obesity and T2DM, frequently co-occur with mood disorders like anxiety and depression, some scholars have introduced the concept of the metabolic-affective syndrome and suggested that there may be common underlying mechanisms for obesity, T2DM, and depression (11).In-depth mechanistic investigations have revealed that the pathological network underlying metabolic affective syndrome encompasses multiple pathways, such as neuroendocrine dysregulation, chronic low-grade inflammation, and insulin resistance, as well as other factors (12, 13).Current clinical management demonstrates persistent limitations in the efficacy of conventional antidepressant therapies and glycemic control protocols for patients with T2DM and comorbid depression (14), highlighting the lack of targeted therapeutic strategies for metabolic affective syndrome.

Glucagon-like peptide-1 (GLP-1), a hormone secreted by intestinal L-cells, exhibits glucose concentration-dependent hypoglycemic effects. Its receptor agonists (GLP-1RAs) mimic the physiological actions of GLP-1 and have been widely used as glucose-lowering agents in the clinical management of T2DM, particularly in overweight/obese patients (15, 16). GLP-1RAs and their analogs can cross the blood-brain barrier and directly influence the physiological functions of the human brain (17). Basic studies reveal that GLP-1RAs exert neuroprotective effects through multiple pathways such as inhibiting neuroinflammation, promoting neurogenesis, and restoring neuronal insulin signaling (18, 19). Preclinical studies have shown that liraglutide treatment significantly improves cognitive function in patients with depression and bipolar disorder (20). However, current clinical evidence remains controversial. Although recent meta-analyses support the efficacy of GLP-1RAs in improving depression scale scores (21), some studies suggest potential risks of inducing mood fluctuations or depressive symptoms (22).This inconsistency in evidence reflects the complexity of disease mechanisms and highlights the importance of conducting rigorous clinical studies.

To this end, the project team designed a randomized, controlled, double-blind clinical trial: Effect of Liraglutide on Depressive Symptoms in Overweight or Obese Patients with Type 2 Diabetes: Protocol for a Pilot Randomized Controlled Trial. The findings of this study will offer supportive evidence for liraglutide use in overweight or obese patients with type 2 diabetes mellitus comorbid with depression, and lay the groundwork for a definitive large-scale clinical study.

### Objectives {7}

This study aims to evaluate the clinical efficacy of daily liraglutide treatment in obese and overweight patients with comorbid T2DM and depression as well as its impact on depressive symptoms. This study adopts a multidimensional assessment system: 1) metabolic parameters, with focused monitoring of glycemic control, body weight changes, and insulin sensitivity improvements; 2) mental health evaluation, with dynamic assessments using standardized depression scales combined with resting-state functional magnetic resonance imaging (rs-fMRI) to investigate brain functional alterations; and 3) pathogenesis exploration, with assessment of the changes in inflammatory and oxidative stress markers. The results of this study are expected to demonstrate that liraglutide can improve metabolic parameters and depression scores in overweight or obese patients with T2DM comorbid with depression, providing evidence for GLP-1RA intervention in “metabolic-affective syndrome. Furthermore, through systematic analysis of the aforementioned biomarkers, this study aims to preliminarily elucidate the potential mechanism underlying liraglutide’s benefits—specifically, whether it exerts concurrent positive effects on both metabolism and depressive symptoms via a synergistic pathway involving the reduction of systemic low-grade inflammation, alleviation of oxidative stress, and improvement of insulin signaling.

### Trial design {8}

This randomized, controlled, double-blind pilot trial will be conducted in Chengdu, China. Eligible participants will be randomly allocated to two parallel groups (1:1 ratio). All participants will retain the right to withdraw at any stage, consistent with the Standard Protocol Items: Recommendations for Interventional Trials (SPIRIT) guidelines (23). **Figure 1** presents a flowchart of the study.

**Figure 1 f1:**
[figure not shown]
Flow diagram of the recruitment process, group allocation, and participation in the two interventions.

## Methods: participants, interventions, and outcomes

### Study setting {9}

The investigation will be conducted at a prestigious third-grade Class A medical institution in Shuangliu District, Chengdu. This hospital is recognized as the largest and prominent center for traditional Chinese medicine in the region, serving nearly two million residents. Equipped with state-of-the-art diagnostic and treatment facilities, patients who are enrolled in the study will receive their follow-up care, undergo necessary medical examinations, receive drug interventions, and fill out the required questionnaires within the hospital’s endocrinology department.

### Eligibility criteria {10}

The diagnostic and screening process for depression in this study will be conducted in two stages. Initial screening based on the Hamilton Depression Rating Scale (HAMD-24) will be performed by trained research staff. Subsequently, a definitive diagnosis of depressive disorder will be confirmed by a board-certified psychiatrist with over ten years of clinical experience, using the Mini-International Neuropsychiatric Interview (MINI) aligned with ICD-11 criteria. All raters administering the HAMD will undergo standardized training, and inter-rater reliability will be assessed prior to the main trial using an independent sample; the results (Intraclass Correlation Coefficient) will be reported to ensure consistency. Endocrinologists will be primarily responsible for assessing metabolic inclusion criteria and overall medical safety. The screening protocol will involve an array of assessments to ensure comprehensive evaluation of each participant. These include baseline demographic and anthropometric measurements (height, weight, and body mass index), laboratory investigations (fasting blood glucose levels, glycated hemoglobin levels, complete blood count, and routine biochemical profiles), and psychological evaluations using standardized tools such as the Hamilton Depression Rating Scale. In addition, an exhaustive review of each participant’s medical history will be conducted, and eligible individuals will be provided with a detailed explanation of the aims and objectives of the study. If they indicate a desire to participate, a personal interview will be arranged to address any questions and verify that they meet all specified inclusion and exclusion criteria. In this interview, a member of the research team from the trial steering committee will present the study details to potential participants and obtain written informed consent. Screening will continue until the target number of participants is achieved. **Table 1** lists the inclusion criteria and **Table 2** lists the exclusion criteria.

**Table 1 T1:** Inclusion criteria.

Inclusion of criteria entries	
(1)	Age ≥18 years
(2)	Meeting the diagnostic criteria for Type 2 diabetes (24), with poor glycemic control after lifestyle intervention with 7.0% ≤ glycated hemoglobin ≤ 9.0% and fasting blood glucose ≤ 11.1 mmol/L
(3)	Body mass index greater than 24.0 kg/m²
(4)	Meeting the diagnostic criteria for mild depression without psychotic symptoms (25)
(5)	A score on the Hamilton Depression Rating Scale (HAMD, 24-item version) of ≥8 and ≤35 (26)
(6)	No use of any antidepressant or psychotropic medications in the past two weeks
(7)	The patient’s condition was stable and met the requirements of follow-up evaluation
(8)	Voluntary participation in the trial and signing of an informed consent form

**Table 2 T2:** Exclusion criteria.

Exclusion of criteria entries	
(1)	In cases of combined severe infections or significant functional disorders of crucial organs, such as: ALT or AST ≥ 2.5 times the upper limit of the normal value, or total bilirubin ≥ 2 times the upper limit of the normal value; Impaired renal function: glomerular filtration rate (eGFR, CKD-EPI formula) < 60 mL/min/1.73m2, calcitonin ≥ 50 ng/L; Serum amylase or lipase ≥ 3 times the upper limit of the normal value; Severe arrhythmias, heart failure, etc., are not suitable for participating in the trial
(2)	Those with other severe mental symptoms, such as combined organic mental disorders, alcohol and drug dependence, schizophrenia, bipolar disorder, etc.; Patients with a suicide risk
(3)	Subjects with persistent gastrointestinal symptoms such as nausea and vomiting within 6 months prior to enrollment, a history of gastroparesis, uncontrolled gastroesophageal reflux disease, gastric ulcer or pancreatitis; Currently presenting with diabetic ketoacidosis or diabetic hyperosmolar state
(4)	Subjects with a known history of drug abuse or long-term heavy alcohol consumption, causing physical and mental dependence, with an average daily intake of pure alcohol exceeding 25g (equivalent to 750 mL of beer, 250 mL of wine, or 50g of spirits) within 3 months prior to screening
(5)	Subjects currently participating in other drug clinical trials or having used DPP-4 and GLP-1 related preparations within 3 months.
(6)	Subjects currently suffering from perimenopausal syndrome; Pregnant or lactating women; or those allergic to the trial drug
(7)	Subjects with a previous history of medullary thyroid carcinoma or a family history of type 2 multiple endocrine neoplasia syndrome

### Who will take informed consent? {26a}

Before potential participants are enrolled in the clinical trial, the responsible physician will provide a detailed explanation of all aspects of the study. This information included the nature of the interventions, potential risks related to participation, anticipated benefits, and other relevant details. If participants choose to participate after fully understanding the study, its risks, and potential benefits, they or their legally authorized representatives will sign a written informed consent document to confirm their voluntary agreement to participate.

### Additional consent provisions for collection and use of participant data and biological specimens {26b}

The informed consent process includes participants’ agreement to the use of their personal data as part of the research. No additional analyses will be performed on the biological samples.

## Interventions

### Explanation for the choice of comparators {6b}

The trial is designed as a placebo-controlled study with a 1:1 randomization ratio between liraglutide and placebo. Patients in both study arms will receive a structured dietary management plan and guidance on diabetes-specific physical activity. They will be required to adhere consistently to the prescribed diet and exercise regimen for 12 weeks.

### Intervention description {11a}

#### Randomization and intervention

Upon providing written informed consent, participants will be randomly allocated in a 1:1 ratio to either the experimental or control group. The experimental group will receive active treatment with liraglutide injections, whereas the control group will receive matching placebo injections. Treatment protocols will be determined by two endocrinologists and a psychiatrist involved in screening. Both groups will receive identical standard care, including diabetes-specific dietary plans and exercise guidance throughout the 12-week study period. Outcomes will be assessed at four time points: baseline and weeks 4, 8, and 12 (dual assessment at week 12 for the interim and final evaluations).

#### Experimental group protocol

Participants will initiate liraglutide at 0.6 mg/day for two weeks, with weekly 0.6 mg dose escalation to reach the target dose of 1.8 mg by week 2. Following a 2-week titration phase, the dose will be maintained at 1.8 mg for the remaining 10 weeks. Subcutaneous administration via a prefilled pen will occur daily at self-selected consistent times at preferred injection sites (the upper arm, thigh, or abdomen). For participants intolerant of 1.8 mg, the dose will be temporarily reduced to 1.2 mg, followed by two re-escalation attempts at 2-week intervals. Those who fail both attempts will continue on 1.2 mg.

#### Control group protocol

Placebo recipients will follow identical dosing schedules to the experimental group, including matched titration phases and injection procedures. Dose adjustments will be synchronized between the groups to maintain blinding integrity.

### Criteria for discontinuing or modifying allocated interventions {11b}

Individuals will be removed from the study under specific conditions: 1) participants who consistently violate the study protocol, fail to comply with the medication regimen, or for whom treatment efficacy cannot be determined due to incomplete data; 2) participants who manifest hypersensitivity reactions or are intolerant to the study medication, with special attention to those exhibiting exacerbation of depressive symptoms or suicidal ideation, requiring immediate cessation of study participation and the initiation of psychological intervention; 3) participants who opt to withdraw from the clinical trial and cease treatment; 4) participants in whom the average fasting blood glucose level reaches or exceeds 11.1 mmol/L during follow-up and this threshold is not reduced after a one-week reassessment; and 5) participants exhibiting emergence of acute or chronic pancreatitis, thyroid abnormalities, or other endocrine disorders during the treatment period, or significant deviations in liver function or serum amylase levels beyond the normal range. For all instances where the participants is discontinued, the rationale must be documented, and the corresponding case report forms must be preserved for subsequent review.

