### Strategies to improve adherence to interventions {11c}

Our study team will devise and implement regular communication strategies to enhance the adherence of participants to the research interventions. This strategy will involve weekly communication with participants via WeChat and telephone, which will not only help increase their engagement and enthusiasm for the study, but also will allow us to stay informed about their psychological well-being. Through these communication channels, the research team will closely monitor and identify any potential side effects or adverse events experienced by participants, thereby ensuring the safety and efficacy of the study.

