### Participant timeline {13}

Outcome assessments will be performed at baseline, followed by three subsequent visits. At baseline assessment, we will gather data on patient demographics, including age, gender, educational level, employment status, marital status, and comorbidities. Additionally, we will document the date of initial diagnosis, symptom duration, and details of prior medications and treatment regimens. The participants are required to revisit the hospital at 4, 8, and 12 weeks after medication initiation for a series of evaluations. These include height and weight measurements, completion of pertinent laboratory tests, and the administration of depression and cognitive function scales. These assessments aim to provide a comprehensive evaluation of treatment efficacy. The detailed enrollment process and comprehensive schedule of the evaluation results are presented in **Table 3**.

**Table 3 T3:** Schedule of outcome measures and trial-related activities.

Items	Enrollment day	4 weeks	8weeks	12 weeks
Inclusion screening				
Sign informed consent	*√*			
Record general information	*√*			
Gender	*√*			
Age	*√*			
Body weight	*√*	*√*	*√*	*√*
height	*√*	*√*	*√*	*√*
Waist circumference	*√*	*√*	*√*	*√*
Hip circumference	*√*	*√*	*√*	*√*
Medical history and treatment history	*√*			
Combined disease and medication records	*√*			
life history	*√*			
Safety				
blood routine examination	*√*			*√*
routine urine test	*√*			*√*
stool routine examination	*√*			*√*
liver function	*√*			*√*
renal function	*√*			*√*
Electrocardiograph	*√*			*√*
Adverse events and complications		*√*	*√*	*√*
Efficacy index				
Hamilton Depression Scale 24 scores	*√*			*√*
Blood glucose (fasting and 2 hours after meals)	*√*			*√*
glycosylated hemoglobin	*√*			*√*
blood lipids	*√*			*√*
tumor necrosis factor-α, Interleukin-6	*√*			*√*
super Oxide Dismutase,malondialdehyde	*√*			*√*
HOMA Insulin resistance Index	*√*			*√*
Insulin sensitivity Index	*√*			*√*
HOMA Islet beta Cell Function Index	*√*			*√*
resting-state functional magnetic resonance imaging	*√*			*√*

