### Statistical methods

#### Statistical methods for primary and secondary outcomes {20a}

The aim of this study is to compare the effectiveness of the two treatment regimens by assessing participants twice, once at baseline and again at the 3-month follow-up. To control for potential confounding variables, we will statistically adjust for participants’ age, gender, body mass index, and Hamilton Depression Rating Scale scores in accordance with the STRIVE criteria. Numbers and percentages will be used to express categorical variables and median and interquartile range will be used for continuous variables. Primary outcome measures (e.g., HAMD score, HbA1c, body weight) will be analyzed using Linear Mixed-Effects Models. The models will include treatment group, time, and the group-by-time interaction as fixed effects to test for between-group differences in treatment effect and its change over time. Subject-specific intercepts will be included as random effects. Analyses will be adjusted for pre-specified confounding variables, including age, sex, baseline BMI, and baseline HAMD score, which will be entered into the models as fixed-effect covariates. For missing data due to dropout, Multiple Imputation will be employed. Secondary outcomes and baseline characteristics will be described and compared as originally planned. All analyses will be performed using SPSS v.22.0 (SPSS Inc., Chicago, IL, USA) and the lme4 package in R. A p-value < 0.05 will be considered statistically significant, whereas a p-value <0.01 will be regarded as indicating a high degree of statistical significance.

The DPABI v6.0 toolkit will be used to perform two-sample t-tests on the whole-brain ALFF, ReHo, and VMHC maps of the two groups of participants. To correct for multiple comparisons across voxels, the statistical significance of the resulting maps will be assessed using Gaussian Random Field (GRF) theory, a method for family-wise error (FWE) rate correction. The threshold was set at a voxel-level significance of P < 0.001 and a cluster-level significance of P < 0.05.

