### Methods in analysis to handle protocol non-adherence and any statistical methods to handle missing data {20c}

In this study, we will prioritize the utilization of data provided by participants who discontinue their involvement before the final follow-up. Any incomplete data as a result of participant withdrawal will be categorized as missing, and estimation or imputation methods will not be employed for these missing values.

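### The discontinuation criteria remove randomised participants from the study rather than only from study drug, so the week-12 HAMD, HbA1c and fMRI values are lost, in part perhaps for reasons linked to outcome

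*Protocol article*

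**What the plan says.** Section {11b} of the protocol article opens with "Individuals will be removed from the study under specific conditions". It then lists five grounds:

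1. Persistent protocol violation, and those who "fail to comply with the medication regimen, or for whom treatment efficacy cannot be determined due to incomplete data".
2. Hypersensitivity or intolerance, with particular attention to worsening depression or suicidal ideation, "requiring immediate cessation of study participation and the initiation of psychological intervention".
3. The participant's own choice to withdraw.
4. Mean fasting glucose at or above 11.1 mmol/L that has not come down on recheck a week later.
5. Pancreatitis, thyroid or other endocrine disorders, or marked liver or amylase abnormalities.

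After discontinuation, the section asks only that the reason be documented and the case report form kept.

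In Table 3 (section {13}) the row "Hamilton Depression Scale 24 scores" is ticked at enrolment and week 12 only, as are HbA1c and resting-state fMRI. Section {20a} agrees, describing the comparison as "assessing participants twice, once at baseline and again at the 3-month follow-up". Section {11c} adds weekly contact that "will allow us to stay informed about their psychological well-being".

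On missing data, section {20a} says "For missing data due to dropout, Multiple Imputation will be employed", while section {20c} says "estimation or imputation methods will not be employed for these missing values". Section {20c} also gives priority to using the data of people who discontinue.

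**The concern.** Stopping study drug and leaving the study are different events. A patient can stop the drug for safety and still attend at week 12 for a HAMD rating and a blood sample. Section {11b} merges the two, and because participant choice is a ground of its own, the other four are removals imposed by the trial.

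The abstract names antidepressant effect as the specific focus, and the background section says the pilot is to prepare a definitive trial. If people who deteriorate, stop complying or have incomplete data are taken out before the only post-baseline HAMD, the week-12 comparison may describe those who stayed well and compliant rather than the two groups as randomised. Values never collected cannot be restored by a later analysis plan.

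**Working it through.** **Step 1. The plan's own figure.** Section {14} takes 50 evaluable participants (25 per group) and 10–15% dropout. At 15%, 25/(1 − 0.15) = 29.4, so 30 per group and 60 in total. At 10%, 50/(1 − 0.10) = 55.6, so 56. The stated 60 reproduces at the 15% end and is not in dispute.

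**Step 2. How many people.** 60 × 0.10 = 6 and 60 × 0.15 = 9, leaving 54 to 51 with a week-12 value. Section {14} does not say whether these losses include removals under {11b}.

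**Step 3. What a removed person contributes.**

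| Outcome | Table 3 schedule | Post-baseline value if removed at, say, week 5 |
|---|---|---|
| HAMD, HbA1c, fMRI | enrolment, week 12 | none |
| Body weight (hence BMI) | enrolment, weeks 4, 8, 12 | week 4 |

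Section {11a} and the text of section {13} describe assessments at weeks 4, 8 and 12, the latter including laboratory tests and depression scales. If that text governs, the same person may have a week-4 HAMD or laboratory value. The week-12 value is missing on either reading.

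**Step 4. Which grounds may be linked to outcome.**

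- Ground 2, depression clause: the clearest link, since HAMD measures the same thing. Weekly contact can reveal worsening before any scheduled rating, and no score threshold is named, so no recorded HAMD need explain the removal.
- Ground 1: a possible link. It also makes missing data a reason for removal.
- Ground 4: linked to glucose, but the triggering reading can enter a mixed model if it is recorded, so any bias may be small. The point does not rest on it.
- Grounds 3 and 5, and hypersensitivity: not necessarily linked.

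**Step 5. What can be said about bias.** Let p be the proportion removed in an arm, and d the mean of (unseen week-12 HAMD minus the value the analysis implies for those people). The error in that arm's mean is −p × d. With d equal in both arms, the error in the liraglutide-minus-placebo difference is −(p_L − p_P) × d. Section {14} cites withdrawal rates from other trials:

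- 10% v 2% at 16 weeks: −(0.10 − 0.02) × d = −0.08d. For positive d this favours liraglutide.
- 2/198 v 4/198 at 56 weeks: −(0.0101 − 0.0202) × d = +0.01d, against liraglutide.
- Equal loss: zero.

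These are all-cause withdrawals in other trials, used only to show that the sign is open. The documents do not give d.

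**Step 6. Direction check by simulation, all inputs assumed.** HAMD change has SD 6 and a placebo mean of −3, and everyone who worsens by at least 3 points is removed. A true effect of −2 is then estimated among completers as −1.36, with 16% removed on placebo and 9% on liraglutide. With no true effect but a stricter removal threshold on liraglutide (3 v 5 points; 16% v 9% removed), a spurious benefit of about −0.6 appears. The bias can run either way, and these sizes are not estimates for this trial.

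**The case against.** The strongest reply has five parts.

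- **Interim visits.** Sections {11a} and {13} imply HAMD and laboratory assessments at weeks 4 and 8, so having no post-baseline value follows only from Table 3 and {20a}. This stands. It softens the consequence but does not restore the week-12 value.
- **Link to outcome.** A reader might infer that all the loss is outcome-related. The text does not support that. Several grounds need have no link, and worsening depression is nested under intolerance rather than written as a free-standing trigger. The pool is also narrow: entry requires mild depression, and patients with a suicide risk are excluded. Hence some of the loss may be related, and no more.
- **Partial handling.** Section {11a} keeps people who cannot tolerate 1.8 mg on 1.2 mg, which limits removals for intolerance. Section {20c} wants discontinuers' data used, so removal from the study should not be read as exclusion from the analysis. Both stand, but {20c} can use only what was collected. The two missing-data statements conflict, and neither recovers an uncollected value.
- **Size.** With assumed d of 3 to 10 HAMD points, 0.08d is 0.24 to 0.8 points. With assumed SD 5 to 7 and about 27 v 29 people retained, the standard error is SD × √(1/27 + 1/29), or 1.3 to 1.9, so the shift is roughly 0.13 to 0.6 standard errors. A modest effect in a pilot sized for precision is quite possible.
- **A condensed article.** An early-termination visit could sit in the full protocol. But the point concerns a stated rule, not a missing detail. Staff who followed it as written would end follow-up.

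**Conclusion.** The point holds as a correctable fault in a stated conduct rule. As written, {11b} ends study participation on grounds other than the participant's own choice, and the week-12 HAMD, HbA1c and fMRI values go with it. Under Table 3 and {20a} no post-baseline value for these outcomes remains; under {11a} and the text of {13} interim HAMD or laboratory values may. Some of the loss may be outcome-related, most plausibly through the depression clause, so the week-12 HAMD comparison may not represent the groups as randomised.

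The number affected is unknown. It would be 6 to 9 of 60 only if the planned dropout consisted of such removals. A reader might infer a bias towards liraglutide from the 10% v 2% figures, but the other cited trial gives the opposite sign, and neither size nor direction can be derived. Nor is safety at issue: the stopping rules and adverse-event oversight in {11b} and {22} are unaffected.

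**What to change.** Reword {11b} along these lines: study drug will be stopped if any of the listed safety criteria is met, and the participant stays in the study unless consent is withdrawn. Keep every safety criterion, including psychological intervention for worsening depression or suicidal ideation. Delete non-compliance and incomplete data as grounds for removal. Invite everyone who stops drug to the already scheduled week-12 assessment, with fMRI optional. Analyse their data in the allocated arm, in keeping with the aim of {20c}, and note any rescue glucose-lowering or antidepressant treatment.

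The cost is a change of wording, a few off-drug week-12 visits (about 6 to 9 if losses match the planned rate and all are of this kind), and some dilution of the estimated effect by rescue treatment.
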